## Abstract

**Introduction:** Takotsubo syndrome (TTS) is an acute heart failure syndrome which is preceded by a variety of emotional or physical triggers, with central nervous system conditions being an important trigger. Remote ischemic conditioning (RIC) is a promising interventional treatment based on the probability that both TTS and acute coronary syndrome may respond similarly to interventions. The heart protection effect of RIC has been repeatedly confirmed in animal models and observational clinical trials; however, it has never been studied in patients with TTS after acute stroke in randomized clinical trials with a higher level of evidence. The present study will be a proof-of-concept study to determine whether RIC can reduce cardiac injury and eventually improve the heart function and clinical outcomes of TTS patients after acute stroke.

**Methods and Analysis:** A single-center, outcome-assessor-blinded, randomized controlled trial (RCT) will be conducted to evaluate the effect of RIC in TTS patients after acute stroke. Major eligibility criteria include TTS patients diagnosed with acute stroke, which can be confirmed on computed tomography or magnetic resonance imaging; patients aged 18–75 years; patients admitted to a hospital within 48 h after the onset of acute stroke; and patients diagnosed with Takotsubo cardiomyopathy with an InterTAK diagnostic score ≥50. A total of 60 eligible patients will be randomly allocated into either the RIC or the control group. The primary endpoint is a composite of death from any cause and major adverse cardiac and cerebrovascular events during the in-hospital period and at the 1- and 6-month follow-up.

**Ethics and dissemination:** This study has been approved by the Medical Ethics Committee of Xuanwu Hospital, Capital Medical University ([2017] 072). The study findings will be presented at international conferences and published in a peer-reviewed journal.

**Trial registration:** This study has been prospectively registered in the Chinese Clinical Trial Registry on September 10, 2018 (ChiCTR1800018290).

## Introduction

### Description of the Disease

Takotsubo syndrome (TTS) represents an acute heart failure condition which is often preceded by sudden extreme stresses including emotional or physical triggers (1). A variety of physical stressors have been reported, including acute critical illness, acute respiratory failure, pancreatitis, traumatic injury, and iatrogenic factors such as surgery, exercise tests, diarrhea, or dobutamine stress echocardiography (1, 2). Central nervous system conditions such as stroke, traumatic brain injury, intracerebral hemorrhage, or seizures also represent an important trigger (1). Patients with TTS usually present with acute chest pain, breathlessness, palpitations, sweating, nausea, and congestive heart failure (1, 2) its clinical symptoms are similar to acute coronary syndrome, except demonstrable coronary artery stenosis or spasm (3). TTS is characterized by transient left ventricular dysfunction, which extends to more than one epicardial coronary artery territory, and a disproportionate increase in troponin compared with the diffuse electrocardiographic and cardiac imaging changes (4). Currently, there are no widely accepted diagnostic criteria for TTS. The most widely used criterium was the modified proposed criteria by the Mayo Clinic for the diagnosis of TTS (5). The InterTAK International Registry Group has developed a simple scoring system, the InterTAK diagnostic score (6), that takes into account five historically used clinical variables and two ECG variables. The InterTAK diagnostic score is slightly different from the modified Mayo Clinic criteria (7). Although considered as a fully reversible disease in most cases, TTS has been described in about 52% of cases to be associated with various complications, such as acute congestive heart failure, acute pulmonary edema, shock, and ventricular fibrillation, and it is in acute phase in most cases (8–11).

Several hypotheses have been proposed for the pathogenesis of TTS, including aborted myocardial infarction (MI) with spontaneous recanalization, myocarditis, coronary artery vasospasm, blood-borne catecholamine myocardial toxicity, and autonomic nervous system dysfunction with sympathetic hyperexcitation (12, 13), of which, the involvement of the adrenergic cascade triggered by physical or emotional stress is considered to be the most convincing (14, 15). Additionally, catecholamines can exert a direct catecholamine toxic effect on myocytes, involving the oxidative stress and inflammatory cascades (16), which can cause microvascular dysfunction, thus leading to reduced myocardial perfusion (17).

### Description of the Intervention

Previous studies revealed that both neuronal and humoral components are involved in the signal transfer in remote ischemic conditioning (RIC) treatment; they act in concert and interact on three different levels from the stimulation site to the target organ. Firstly, peripheral sensory nerves are directly activated by the ischemic/reperfusion stimuli and/or indirectly activated by the humoral factors (18). Secondly, the peripheral sensory afferent nerves projecting to the autonomic centers of the central nervous system eventually activate efferent vagal nerves (18), which subsequently release acetylcholine to directly activate receptors in the target organs and/or activate receptors in other organs that can release humoral factors to indirectly act on the target organs (19). Finally, the intrinsic nervous system and the response of the specific parenchymal cells of the target organ are activated to contribute to the final effect (19, 20). Though transient receptor potential vanilloid 1 (TRPV1), calcitonin gene-related peptide (CGRP), substance P, and other mediators were found to be involved in RIC, the exact mechanisms of these pathways are still far from clear (18, 21–23). In this present study, a preliminary exploration on the changes in cardiac biomarkers will be made after RIC treatment; however, more basic research is still required to clarify the specific mechanism.

### Rationale for the Present Study

Though the role of myocardial stunning in the mechanism of TTS is still unclear, some therapeutic algorithms have been developed for the treatment of TTS patients (1) based on the probability that both TTS and acute coronary syndrome may respond similarly to pharmacological or other interventions (24), among which, RIC is a promising intervention treatment. Ischemic conditioning was first recognized in 1986, when it was discovered that brief interruption of blood supply to a vascular territory limits the extent of ischemia, reperfusion injury, and the eventual size of the MI (25). Soon after, it was found that the brief and complete interruptions of blood supply to a particular vascular territory provide benefits to other vascular territories to a certain extent (26–29). Since then, the heart protection effect of RIC has been repeatedly confirmed in various animal models (30–36). Furthermore, several clinical studies have also shown the beneficial effects of RIC on heart injuries, such as ST-segment elevation myocardial infarction (37, 38), and heart failure after primary percutaneous coronary intervention (39). However, the heart protection effects of RIC have not been observed in all patients with heart injuries. Kahlert et al. reported that RIC provided no protection effect on the heart before transfemoral transcatheter aortic valve implantation in the interim analysis of a randomized controlled trial (RCT) (40). In particular, RIC has never been studied in patients with TTS patients after acute stroke. Therefore, whether RIC can benefit TTS patients after acute stroke still needs to be clarified.

### Objectives

The present study will be a proof-of-concept study to determine whether RIC can exert a heart protection effect and thereby reduce cardiac injury and eventually improve the heart function and clinical outcomes of TTS patients after acute stroke.

## Methods and Analysis

### Overall Design

A single-center, outcome-assessor-blinded, randomized controlled trial will be conducted in the Neurosurgical Intensive Care Unit (NICU) of Xuanwu Hospital, a tertiary neurosurgical referral centre in Beijing, China, and aims to evaluate the effect of RIC on TTS in patients with acute stroke. This protocol has been developed according to the Standard Protocol Items: Recommendations for Interventional Trials (SPIRIT) (41). The conduction and reporting of this RCT will follow the Consolidated Standards of Reporting Trials (CONSORT) statement and its extension to non-pharmacological interventions (42). The study process is summarized in Figure 1.

**Figure 1 F1:**
[figure not shown]
Study flow diagram according to CONSORT 2010. *SAH*, subarachnoid hemorrhage; *RIC*, remote ischemic conditioning; *ECG*, electrocardiograph; *EchCG*, echocardiograph; *mRS*, modified Rankin Scale; *GOS*, Glasgow Outcome Score.

### Eligibility Criteria

Adult patients with acute stroke referred to the NICU will be screened for trial eligibility. Routine ECG, echocardiography, and serum examination of cardiac injury biomarkers will be performed. Based on the InterTAK diagnostic score (6), patients diagnosed with TTS (InterTAK diagnostic score ≥50) will be recruited into this study. At least two physicians will review the eligibility criteria, and a third senior physician will resolve any disagreement. The inclusion and exclusion criteria are summarized as follows:

#### Inclusion Criteria

Patients diagnosed with acute stroke (ischemic or haemorrhagic), which can be confirmed on computed tomography (CT) or MRI;Patients diagnosed with subarachnoid hemorrhage with Hess–Hunt grades I–IV;Patients aged 18–75 years;Patients admitted to hospital within 48 h of acute stroke onset;Patients diagnosed with Takotsubo syndrome with an InterTAK diagnostic score ≥50 (6). The ventricular wall motion will be evaluated with echocardiography. If acute coronary syndrome (ACS) is suspected based on ECG, echocardiography, or biomarker findings, coronary computed tomography angiography (CTA) will be conducted to rule out ACS. Coronary angiography and cardiac magnetic resonance imaging will be utilized to differentiate ACS only when necessary.Patients with a signed written informed consent form.

#### Exclusion Criteria

Acute stroke is not the major cause for admission or the patient is receiving palliative care.The patients suffer from concurrent diseases, such as severe cardiovascular disease, are in an extremely critical condition, have cerebral hernia, and/or it is highly expected that the patients will fail to complete the study.The patients are admitted to the hospital more than 48 h after acute stroke onset or have any subsequent stroke after the diagnosis of TTS.The patients have concurrent limb vascular occlusive disease and/or other diseases or conditions which cause intolerance to the intervention treatment.Both upper limbs of the patients are affected by the stroke, indicated by any symptoms, abnormal results of physical examination, or neurophysiologic tests in any upper limbs.The patients have other conditions that are not suitable for RIC treatment, such as skin damage, severe thrombocytopenia, and abnormal blood clotting.

### Randomization and Blinding

A total of 60 eligible patients with acute stroke, in accordance with the inclusion and exclusion criteria, will be included in this study. Random numbers will be generated on a computer by an unblinded physician who will not be involved in the data analysis and then placed in sealed envelopes. The patients will be randomly allocated into either the RIC or the control group according to a ratio of 1:1. The physician responsible for performing RIC will not be blinded and will play no further role in the clinical trial; the staff responsible for the data collection and analysis will be blinded. Hence, this is an outcome-assessor-blinded study.

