### Patient and Public Involvement

The protocol of this study was discussed and developed by a multidisciplinary team of experts including epidemiologists, clinicians, and statisticians; however, no patients or public people were involved in the design phase.

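### The allocation list is made by an unblinded physician kept apart only from data analysis, and stroke type is neither a named stratification factor nor in the stated model list

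*Protocol article*

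**What the plan says.** All references are to the protocol article.

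- **Sequence and concealment (Randomization and Blinding).** "Random numbers will be generated on a computer by an unblinded physician who will not be involved in the data analysis". For concealment, the numbers go into envelopes, which the text describes as sealed. Patients are "randomly allocated into either the RIC or the control group according to a ratio of 1:1". No stratification factor is named.
- **Separation of roles (same section).** For the person who delivers the intervention, the text is stricter: "The physician responsible for performing RIC will not be blinded and will play no further role in the clinical trial". No such bar is stated for the person who makes the list. The text does not say whether the two are the same person.
- **Who decides eligibility (Eligibility Criteria; Exclusion Criteria).** At least two physicians review each patient, and a third, senior one settles disagreements. Some exclusions call for judgement: how critical the patient's state is, whether the patient is likely to complete the study, and whether the patient is suited to remote ischaemic conditioning (RIC).
- **Population (Inclusion Criteria).** "Patients diagnosed with acute stroke (ischemic or haemorrhagic"; SAH is covered by its own grade limits.
- **Model variables (Data Management and Statistical Analysis).** The initial model lists demographic and risk factors, cardiac biomarkers, uric acid, ejection fraction, LVEDD, mRS and GOS at baseline. Stroke type is not among them.
- **Team (Patient and Public Involvement).** The protocol was developed by "a multidisciplinary team of experts including epidemiologists, clinicians, and statisticians".

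**The concern.** There are two linked weaknesses.

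**Concealment.** Concealment protects the decision to enrol. It requires that nobody who knows the coming assignments can influence who is screened, judged eligible or handed an envelope. Keeping the list-maker out of the analysis does nothing for that. In one intensive care unit, with judgement-based exclusions and controls who receive no RIC, a physician who knew the next assignment could apply those exclusions differently by arm. Blinded outcome assessment cannot undo selection that happened before allocation. All-cause death is part of the primary composite, so steering sicker patients to one arm would act directly on it.

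**Stroke type.** Ischaemic stroke, intracerebral haemorrhage and SAH can be expected to differ in prognosis and in cardiac injury. In a 60-patient trial, a chance difference in their mix can be large enough to cloud the result. As written, neither the allocation nor the stated model deals with it.

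**Working it through.** **1. Concealment (no arithmetic applies).** Set the two role descriptions side by side. The physician who performs RIC has no other part in the trial. The physician who makes the list is kept only from the analysis. The bar that concealment needs (no screening, no enrolment, no envelope handling) appears for neither in those terms, and the general bar that would cover it is given only to the RIC physician. The discussion of limitations likewise addresses only the RIC physician's lack of blinding.

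**2. Chance imbalance in stroke type.** The plan gives no figure to reproduce here.

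Inputs from the document: 60 patients, 1:1, 30 per arm (Randomization and Blinding; Sample Size). Assumed, because the document gives no mix: the minority stroke type makes up 10–50% of patients, that is *m* = 6 to 30 of 60.

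- *Fixed 30:30, unstratified.* The number *X* of minority-type patients in one arm is hypergeometric (60, *m*, 30), and the between-arm difference is |2*X* − *m*|/30. By hand for *m* = 6: a 20-point difference needs *X* = 0 or 6, so P = 2 × C(30,6)/C(60,6) = 2 × 593,775/50,063,860 = 2.4%.
- *Simple allocation.* Each patient has probability 0.5; 200,000 simulated trials.

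| Minority type (assumed) | P(difference ≥ 20 points), simple | Same, fixed 30:30 |
|---|---|---|
| 10% | 0.9% | 2.4% |
| 20% | 6.1% | 10.4% |
| 30% | 9.8% | 15.8% |
| 40% | 12.9% | 18.7% |
| 50% | 15.5% | 19.6% |

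The range is therefore about 1–20%. Forcing equal arm sizes does not remove the risk, so the point does not depend on which kind of unstratified list is used.

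**3. What a 20-point imbalance does to an unadjusted test.** Assumed: stroke type shifts a continuous outcome by 1 SD, and RIC has no effect. The expected difference between arms is then 0.20 × 1 SD = 0.20 SD.

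A quick calculation treats this as a shift of 0.20/√(2/30) = 0.20/0.258 = 0.775 standard errors. It gives P(Z > 1.96 − 0.775) = P(Z > 1.185) = 11.8%. This is too high, because the SD that the t-test estimates also contains the stroke-type variance that the scenario assumes.

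For 18 versus 12 minority-type patients and a within-type SD of 1:

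- between-type variance in each arm: 0.6 × 0.4 = 0.24, or 0.24 × 30/29 = 0.248 as the sample variance estimates it;
- estimated standard error: √(2 × 1.248/30) = 0.288;
- true standard error given these counts: √(2/30) = 0.258;
- P(Z > (2.002 × 0.288 − 0.20)/0.258) = P(Z > 1.46) ≈ 7.2%.

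Simulating the t-test itself (200,000 runs, 30 per arm, one-sided 2.5%) gives slightly more than this approximation:

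| Imbalance | 1 SD = within-type SD | 1 SD = total SD |
|---|---|---|
| 18 v 12 | 7.7% | 8.4% |
| 12 v 6 | about 8.2% | about 9.0% |

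So the conditional figure is about 8–9%. Averaged over all allocations, the one-sided error remains about 2.5%.

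**The case against.** The strongest reply is that a journal article condenses a fuller protocol, and that the section on Quality Control and Safety Assessment promises a manual covering recruitment, eligibility and randomization in detail. The envelopes are stated to be sealed. At least two physicians review eligibility, so one person could not easily steer enrolment. Nothing says that the list-maker screens or enrols. If that person is also the physician who performs RIC, the broader bar already applies. Several baseline covariates in the model (biomarkers, ejection fraction, mRS, GOS) may absorb part of a stroke-type difference.

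Much of this stands, and it limits the point. A reader might infer any of the following, and the document does not support them:

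- *Concealment is broken.* The text does not put the list-maker in contact with enrolment; it only fails to rule that out.
- *Allocation is simple and unblocked, or the envelopes are deficient.* Both would be read from silence. Block size, opacity and numbering are details that an article commonly leaves out, and they are no finding here.
- *The chance imbalance biases the trial.* Randomization holds the error rate at its nominal level on average. The 8–9% applies only once an imbalance of that size has occurred, and only to the arm it favours.
- *The false-win chance is about 12%.* That figure leaves the stroke-type variance out of the test's SD.

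What the reply does not remove is what the article itself states: the list is made by an unblinded physician, the only separation given is from the analysis, and the listed model variables omit stroke type.

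**Conclusion.** The concern holds in limited form. Concealment is insufficiently assured, because the stated separation of the list-maker is not the one that protects enrolment. Stroke type, an evident source of heterogeneity in this population, is handled neither by a named stratification factor nor by the stated model.

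The risk of a 20-point imbalance is about 1–20%, over an assumed minority share of 10–50% and under either simple or fixed 30:30 allocation. Given such an imbalance and an assumed 1 SD effect of stroke type, the unadjusted one-sided false-win chance goes from 2.5% to about 8–9%. Neither the mix nor the effect of stroke type is given in the document, so these figures show scale and are not forecasts. The consequence is lost precision and credibility, not systematic bias. The change is worth making because it costs so little.

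**What to change.** 1. Have a statistician on the team, with no patient contact, generate the allocation list.
2. State that anyone who knows the list takes no part in screening, eligibility decisions or enrolment, and say who holds the sealed envelopes.
3. Stratify allocation by stroke type (ischaemic versus haemorrhagic, including SAH).
4. Include stroke type as a prespecified factor in the analysis, instead of leaving it outside the candidate list or subject to the univariable p < 0.10 screen.

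The sample size stays at 60. Imaging-confirmed stroke is already an entry criterion, and the team already includes statisticians. The small cost is keeping two envelope series instead of one.

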### Intervention and Follow-Up

All eligible patients in the RIC and control groups will receive routine monitoring and medical treatment. Moreover, the patients in the RIC group will receive RIC treatment through an electric auto-control device that has been delineated by Ji et al. (patent number ZL200820123637.X, China): (43) a blood pressure cuff will be placed around the upper arm of the patient and inflated to a pressure of 200 mmHg (44) for 5 min and then deflated for reperfusion for 5 min. The inflation and deflation will be performed for four cycles each time, three times a day for a total of five consecutive days. If an upper limb is affected by the stroke, the other normal upper limb will be selected for RIC treatment. Blood samples will be collected before RIC treatment, every 48 h after RIC treatment until discharge from the NICU. The patients in the control group will not receive RIC treatment; however, blood samples will be collected at the same time points as those in the RIC group. Blood samples will be used for the detection of the following biomarkers: cardiac troponin I (cTnI), N-terminal pro B-type natriuretic peptide (NT-pro BNP), high-sensitivity C-reactive protein (HS-CRP), interleukin-6 (IL-6), interleukin-10 (IL-10), interleukin-17 (IL-17), plasminogen activator inhibitor-1, plasma tissue plasminogen activator, micro-RNA-126, micro-RNA-155, serum nitric oxide (NO), blood uric acid, white blood cell count, and platelet aggregation rate. The electrocardiograph and echocardiography will be performed simultaneously every 48 h after RIC treatment until discharge from the NICU to evaluate the cardiac indicators such as ECG ST segment, percent of arrhythmia, ejection fraction, and left ventricular end-diastolic diameter (LVEDD). All eligible patients will be followed up by core team members based on clinical visits, medical records, or telephone interviews at 1 and 6 months after discharge and undergo the aforementioned examinations and serological tests (Table 1).

**Table 1 T1:** Data collection timeline.

	**Cardiac examination (electrocardiograph, echocardiography)**	**Blood samples**	**Patients' characteristics (mRS or GOS)**	**Clinical outcomes**
At admission	✓	✓	✓	
Before RIC	✓	✓		
Every 48 h after RIC	✓	✓		
At discharge from NICU	✓	✓	✓	✓
At 1 month after discharge	✓	✓	✓	✓
At 6 months after discharge	✓	✓	✓	✓

*RIC, remote ischemic conditioning; NICU, neurosurgical intensive care unit; mRS, modified Rankin Scale; GOS, Glasgow Outcome Score*.

### Quality Control and Safety Assessment

We will develop a manual describing in detail all aspects of the recruitment, eligibility criteria, randomization, interventions, data collection, and case record form (CRF) completion. All staff involved in this trial will be trained beforehand. This manual will be utilized to monitor adherence to procedural steps. Each cuff inflation/deflation time will be recorded to monitor adherence to the intended intervention. The study process will be supervised by an independent data monitoring committee. RIC is a non-invasive means to treat TTS patients by performing repeated inflation and deflation of a blood pressure cuff around the upper arm. However, it should be taken into account that there will be some possible adverse events, such as transient discomfort and/or ischemic damage of the upper arm during compression of the cuff, the formation of ecchymosis on the upper arm after RIC treatment, and new or aggravating neurological deficits during or after RIC treatment. Any serious adverse events possibly related to RIC treatment will be reported to the ethical committee.

